#### Adoption

Adoption will be assessed by describing the proportion, characteristics, and representativeness of Canadian settings approached and those willing to participate in the BETTER 2 program. We will describe the national/provincial/territorial characteristics of the sites, including their similarities and differences relative to other communities in a larger geographic area or region.

#### Implementation

Implementation of BETTER 2 in the diverse primary care settings will be captured by detailed description of the contextual adaptations of the program, the time required for intervention, and the costs of the intervention. In addition, the ‘Qualitative Evaluation’ section details the qualitative approach aimed to capture implementation information including process, facilitators and barriers, and contextual issues.

An economic assessment will include the following:A description of the implementation cost of the intervention in various settings including the amount of time the prevention practitioners spend with individual patients and the improvement in CDPS activities achieved by the various patient populations in the intense intervention groups.We will explore the impact of the different levels of interventions on the costs of the program and examine patterns in costs over time.

#### Maintain

We will explore the extent that the program becomes part of a routine practice and policy over time including how and if the program can be delivered over the long term. Most decisions about maintaining a program are influenced not only by the overall impact of a treatment but also by its costs [21]. The time and cost of the intervention will be captured as described above.

Evaluation of maintenance will include the following:The proportion of primary care providers introduced to the BETTER 2 approach who use the BETTER tools/activities calculated at three time points (see Figure 4, the BETTER 2 timeline).
The proportion of primary care providers introduced to the BETTER 2 approach that adapt the BETTER patient-level intervention, a prevention practitioner health-care professional, into their practices calculated at three time points (see Figure 4, the BETTER 2 timeline).

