**The BETTER 2 timeline.**

### Qualitative evaluation

A qualitative evaluation will contribute to the overall program evaluation of the BETTER 2 program and is aimed at understanding the facilitators and barriers, benefits, and disadvantages of the BETTER approach in varied settings including remote, rural, and disadvantaged populations. A qualitative evaluation will help to examine the uptake of the BETTER 2 program by involving perspectives of those who use and provide the program: health-care providers, administrators, and patients. Data collection strategies include semi-structured interviews (one-on-one interviews, focus groups, and patient feedback forms) with participants (as identified above) by a trained researcher at approximately three time periods throughout the project [25] (see Figure 4, the BETTER 2 timeline).

The goal of the BETTER 2 qualitative evaluation component is twofold. One aim is to facilitate and assist with implementation through the early identification and intervention of potential barriers to the program. The secondary goal is to determine the approach’s adaptability, sustainability, and perceived impact in primary care settings. We will capture how the approach was implemented and adapted to various settings, the impact on patients and practice including any perceived benefits or disadvantages, the feasibility of the approach, and how and if the approach will be sustained. We will explore how the tools/activities were adapted to various primary care settings including perceptions of how well these adaptations worked. We will also consider the contextual factors of the implementation of the program, specifically barriers and enablers to program implementation.

The primary qualitative research questions areWhat is the impact of BETTER 2 on the health setting in each community?How has BETTER 2 been adapted in each community?What barriers and enablers are key to implementation of BETTER 2?How can BETTER 2 be improved?

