### Trial status

The BETTER 2 is a program evaluation and not a research trial. The BETTER 2 program has received approval for the various research components of the program evaluation through the University of Alberta, and St. John’s Newfoundland ethics boards. The program also has a scientific research license with the Northwest Territories. The registration number of the original RCT BETTER trial was ISRCTN07170460.

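### The two maintenance proportions are repeated uptake measures, not conditional on earlier use, so on their own they cannot separate continued use from new uptake

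*Protocol article*

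**What the plan says.** The Maintain subsection of the protocol article (under Program evaluation using the RE-AIM framework) sets its question as follows: "We will explore the extent that the program becomes part of a routine practice and policy over time including how and if the program can" (the sentence ends by asking about long-term delivery). It then opens a list with "Evaluation of maintenance will include the following" and names two quantitative measures:

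- **Tools.** "The proportion of primary care providers introduced to the BETTER 2 approach who use the BETTER tools/activities calculated at three time points".
- **Role.** The proportion of "primary care providers introduced to the BETTER 2 approach that adapt the BETTER patient-level intervention", that is, the prevention practitioner, at the same number of time points.

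Both refer to Figure 4 for the timing; that figure was not available for this review. The subsection adds: "The time and cost of the intervention will be captured as described above". Separately, the Qualitative evaluation section will examine "the feasibility of the approach, and how and if the approach will be sustained", using interviews, focus groups and feedback forms at about three periods.

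The Reach subsection lists a related quantity: among providers or sites approached and educated, the share that have taken up the tools or the role. It gives no repeat time points.

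**The concern.** Maintenance asks whether those who took up the programme keep it going. To answer that with a proportion, one must know who was using it before. The two listed measures do not use that information. At each time point the numerator pools continuing users with providers who have just started, and the remainder pools drop-outs with providers who never started.

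A reader who sees a flat or rising series would naturally take it as evidence that the programme has become routine. The same series could come from substantial abandonment offset by fresh uptake. Conversely, a falling series could come from slow uptake among recently introduced providers while every earlier user continues. The article's Discussion presents sustainability outside a research setting as something the evaluation should inform, so this ambiguity falls on a central message.

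**Working it through.** The article states no sample size, provider count or target for maintenance, so there is no figure to reproduce. The check asks how much the planned proportions reveal about retention. **All counts below are illustrative assumptions.**

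**Notation.** u1 = users at the first time point; n2 = providers introduced by the second; u2 = users at the second; r = first-time-point users still using at the second.

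**Bounds.** The u2 users consist of r continuing users and u2 − r others, who must come from the n2 − u1 providers not using at the first time point. Hence

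max(0, u2 − (n2 − u1)) ≤ r ≤ min(u1, u2), and retention = r / u1.

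**A. Fixed denominator, same proportion at both times**

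| Users / introduced, both times | Measure | Lowest r | Highest r | Retention |
|---|---|---|---|---|
| 20/40 | 50%, 50% | max(0, 20 − 20) = 0 | 20 | 0% to 100% |
| 10/20 | 50%, 50% | max(0, 10 − 10) = 0 | 10 | 0% to 100% |
| 16/20 | 80%, 80% | max(0, 16 − 4) = 12 | 16 | 12/16 = 75% to 100% |

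In general, for a flat proportion p with a fixed denominator, the lowest possible retention is max(0, 2p − 1)/p. At p = 0.8 this is 0.6/0.8 = 75%. At p of 50% or less it is zero, so a flat series sets no lower limit on retention.

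**B. Growing denominator, 20 introduced at first and 40 by the second time point**

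Start from 10/20 = 50%.

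- At 20/40 = 50%, the lowest r is max(0, 20 − 30) = 0 and the highest is 10, so retention is again 0% to 100%.
- Apparent stability: 4 of the 10 early users continue and 16 of the 20 new providers start. The measure is (4 + 16)/40 = 50%, unchanged; retention is 4/10 = 40%.
- Apparent decline: all 10 early users continue and 2 of the 20 new providers start. The measure is (10 + 2)/40 = 30%, down from 50%; retention is 10/10 = 100%.

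**Reading.** Case A shows that the difficulty does not need a growing denominator. Case B shows that growth adds a second way to mislead, in the opposite direction. The proportions are not empty: high values narrow the range, as at 80%. They do not identify retention.

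**The case against.** The strongest reply has four parts.

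1. **Moving denominator.** A reader might infer that the measures divide by everyone ever introduced, with the total rising as the programme expands. The documents do not establish this. The text says only that providers were introduced. The Aims section describes new jurisdictions but gives no calendar of introductions. This part stands, so growth is treated above as one of two possibilities.
2. **Sustainability is addressed elsewhere.** A reader might conclude that the evaluation cannot show whether the programme is sustained, or has no maintenance measure at all. That is too strong: the list of measures is open, time and cost are captured, and the interviews explore sustainment directly. This stands too, but none of these sources yields a retention proportion.
3. **Duplication of Reach.** A reader might say that the maintenance measures simply repeat the Reach proportion. The overlap is only partial. Reach counts those that have adopted, without repeat time points, whereas the first maintenance measure counts use at three.
4. **Legitimacy and level of detail.** The share of introduced providers using the programme over time is a reasonable description of how routine it has become, and retention alone leaves out never-adopters and late adopters. This is also a condensed article, and "BETTER 2 is a program evaluation and not a research trial". These points argue for keeping the existing proportions and for a modest tone. They do not remove the difficulty, because the article does state what the maintenance measures are, and as stated they are not conditional on earlier use. Retention might be derivable if providers are tracked individually, but the article does not plan it.

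**Conclusion.** The point holds in a limited form. The two stated quantitative maintenance measures are repeated cross-sectional uptake proportions. Alone, they cannot separate continued use from new uptake, whether the group introduced is fixed or growing. With a fixed denominator, a flat value of 50% or below is compatible with any retention from 0% to 100%; at 80% the range narrows to 75% to 100%. These ranges follow from counting, but the counts are assumed, and nothing in the article indicates how much drop-out to expect.

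The conclusion concerns these two measures only. It does not say that the evaluation as a whole is silent on sustainability, nor that the denominator is known to grow. It is a cheap and worthwhile improvement, not a flaw that invalidates the evaluation.

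**What to change.** - Keep both existing proportions, but label them as uptake at each time point.
- Add a retention proportion, separately for the tools and for the prevention practitioner role: of the providers using it at one planned time point, the proportion still using it at the next. Three time points give two such intervals. Report it by time since introduction.
- State whether providers introduced means a cumulative total or a fixed cohort. If cumulative, give the number newly introduced at each time point.
- Read the retention figures alongside the cost and interview findings already planned.

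**Cost.** No further time points are needed. Each provider's status must be recorded under an identifier that links the three time points; the article does not say whether this is already done. Retention denominators may be small, especially once split by time since introduction. With an assumed 10 earlier users, one provider moves the figure by 1/10 = 10 percentage points, so counts should be shown beside the percentages.

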**Figure 4 Fig4:**
[figure not shown]
**The BETTER 2 timeline.**

### Qualitative evaluation

A qualitative evaluation will contribute to the overall program evaluation of the BETTER 2 program and is aimed at understanding the facilitators and barriers, benefits, and disadvantages of the BETTER approach in varied settings including remote, rural, and disadvantaged populations. A qualitative evaluation will help to examine the uptake of the BETTER 2 program by involving perspectives of those who use and provide the program: health-care providers, administrators, and patients. Data collection strategies include semi-structured interviews (one-on-one interviews, focus groups, and patient feedback forms) with participants (as identified above) by a trained researcher at approximately three time periods throughout the project [25] (see Figure 4, the BETTER 2 timeline).

The goal of the BETTER 2 qualitative evaluation component is twofold. One aim is to facilitate and assist with implementation through the early identification and intervention of potential barriers to the program. The secondary goal is to determine the approach’s adaptability, sustainability, and perceived impact in primary care settings. We will capture how the approach was implemented and adapted to various settings, the impact on patients and practice including any perceived benefits or disadvantages, the feasibility of the approach, and how and if the approach will be sustained. We will explore how the tools/activities were adapted to various primary care settings including perceptions of how well these adaptations worked. We will also consider the contextual factors of the implementation of the program, specifically barriers and enablers to program implementation.

The primary qualitative research questions areWhat is the impact of BETTER 2 on the health setting in each community?How has BETTER 2 been adapted in each community?What barriers and enablers are key to implementation of BETTER 2?How can BETTER 2 be improved?

### Theoretical frameworks

The BETTER 2 program involves implementation of a CDPS approach into various clinical settings which can be impacted by the health system at various levels, that is, 1) national and provincial (macro), 2) regional or program (meso), and 3) site or clinic (micro) levels [26]. There are numerous models available to inform dissemination and implementation of research [3,27]; however, many miss important constructs or address only one level. Upon reviewing several frameworks, we identified three that could inform our qualitative evaluation at the macro, meso, and micro health system levels including the theoretical domains framework (TDF) [28,29], the consolidated framework for implementation research (CFIR) [3], and the awareness, desire, knowledge, ability and reinforcement (ADKAR) model [30].

The TDF is a comprehensive framework that includes all of the important constructs of implementation [28,29]. Since it is inclusive and addresses a large number of domains (14) and constructs (84), it may not be the best tool to identify and prioritize the key elements of the implementation. However, an awareness of the constructs in the TDF will help ensure that no important construct is missed during the qualitative evaluation. The CFIR is composed of five major domains that capture the characteristics of the 1) intervention, 2) outer setting, 3) inner setting, 4) individuals involved, and 5) process of implementation [3]. The CFIR framework is a pragmatic synthesis of several frameworks and models and will inform the implementation process by identifying key elements in the program implementation in a systematic way. At the micro level, the qualitative evaluation will be informed by the ADKAR model, a model that focuses on change processes on the ‘people level’ and is commonly used in business, government, and community settings [30].

### Trial status

The BETTER 2 is a program evaluation and not a research trial. The BETTER 2 program has received approval for the various research components of the program evaluation through the University of Alberta, and St. John’s Newfoundland ethics boards. The program also has a scientific research license with the Northwest Territories. The registration number of the original RCT BETTER trial was ISRCTN07170460.

## Discussion

The prevalence of chronic disease is steadily increasing [1,2], and this epidemic of chronic disease threatens the sustainability of health-care systems internationally. The BETTER trial, a pragmatic randomized controlled trial, demonstrated the effectiveness of a CDPS intervention that involved prevention practitioners in the primary care multidisciplinary team settings [5]. The intervention could be adapted to become sustainable in the non-research setting. The BETTER 2 program has been funded to bring together research, practice, and policy, through an approach to CDPS that includes the end users. This approach of engaging research, practice, and policy creates a better fit between the information and the needs of the users, a key to integrated knowledge translation [8–11]. This collaborative approach is grounded in practice and developed from existing work.

Our ultimate long-term outcomes are improved clinical outcomes and reduced burden of chronic disease through improved early detection of cancers (e.g., breast, cervical, and colon); lower incidence of cancers through modification of lifestyle (e.g., lung cancer); and reduction of chronic disease through prevention (e.g., diabetes, heart attack, stroke). Cost-effective analyses of the original BETTER trial demonstrated that a prevention practitioner ‘can improve the implementation of clinically important prevention and screening for chronic diseases in a cost-effective manner’ [5]. We expect that achieving these objectives using the BETTER 2 program will lead to cost savings and therefore improved sustainability of the health-care system. The program evaluation as outlined in this paper is designed to provide an understanding of the issues impacting the implementation of an effective approach for CDPS within primary care that may be adapted to become sustainable in the non-research setting. The RE-AIM framework informs our evaluation which includes a composite index to assess effectiveness in real-world settings [5,21,22,24].

## Abbreviations

ADKAR: Awareness, desire, knowledge, ability and reinforcement framework
BETTER trial: Building on Existing Tools to Improve Chronic Disease Prevention and Screening in Family Practice (a pragmatic randomized controlled research trial in family practice settings)
BETTER 2: Building on Existing Tools to Improve Chronic Disease Prevention and Screening in Primary Care (a program aimed to implement the BETTER interventions in expanded settings to improve CDPS in primary care)
CDPS: Chronic disease prevention and screening
CFIR: Consolidated framework for implementation research
CLASP: Coalitions linking action and science
CPAC: Canadian partnership against cancer
CWG: Clinical working group
TDF: Theoretical domains framework
